## Abstract

**Background:**

Music therapy is a standard palliative care service in many pediatric and adult hospitals; however, most research has focused on the use of music to improve psychosocial dimensions of health, without considering biological dimensions. This study builds on prior work examining psychosocial mechanisms of action underlying an Active Music Engagement (AME) intervention, designed to help manage emotional distress and improve positive health outcomes in young children with cancer and parents (caregivers), by examining its effects on biomarkers of stress and immune function.

**Methods:**

This two-group randomized controlled trial (R01NR019190) is designed to examine biological mechanisms of effect and dose-response relationships of AME on child/parent stress during the consolidation phase of Acute B- or T-cell Lymphoblastic Leukemia (ALL) and T-cell Lymphoblastic Lymphoma (TLyLy) treatment. Child/parent dyads (n = 228) are stratified (by age, site, risk level) and randomized in blocks of four to the AME or attention control condition. Each group receives one session (30-minutes AME; 20-minutes control) during weekly clinic visits (4 weeks standard risk B-cell ALL; 8 weeks high risk B-cell ALL/T-cell ALL/TLyLy). Parents complete questionnaires at baseline and post-intervention. Child/parent salivary cortisol samples are taken pre- and post-session (sessions 1–4). Child blood samples are reserved from routine draws before sessions 1 and 4 (all participants) and session 8 (high risk participants). We will use linear mixed models to estimate AME’s effect on child/parent cortisol. Examining child/parent cortisol as mediators of AME effects on child and parent outcomes will be performed in an ANCOVA setting, fitting the appropriate mediation models using MPlus and then testing indirect effects using the percentile bootstrap approach. Graphical plots and non-linear repeated measures models will be used to examine dose-response relationship of AME on child/parent cortisol.

**Discussion:**

During pediatric cancer treatment there are special challenges that must be considered when measuring cortisol and immune function. In this manuscript we discuss how we addressed three specific challenges through our trial design. Findings from this trial will increase mechanistic understanding of the effects of active music interventions on multiple biomarkers and understanding of dose-response effects, with direct implications for clinical practice.

**Trial Registration:**

ClinicalTrials.gov: NCT04400071.

**Supplementary Information:**

The online version contains supplementary material available at 10.1186/s12906-023-03909-w.

## Background

Music therapy has become a standard palliative care service in many pediatric and adult hospitals in the United States [1]. According to a survey of Children’s Hospital Association members, about 70% of the 245 hospitals surveyed reported offering music therapy services to their patients and families [2, 3]. Cancer treatment is an inherently stressful experience for both young children and their parents and their outcomes are interrelated [4–7]. Both children and parents experience emotional distress and poor quality of life, and many parents experience traumatic distress symptoms because of their child’s cancer diagnosis and treatment [8–12].

Although positive outcomes resulting from psychosocial interventions have been associated with improvements in biological function including decreased cortisol production and improved immune function [13–19], most music therapy research has focused on psychosocial dimensions of the cancer treatment experience, rather than its biological dimensions [20–22]. Coupled with growing evidence that active music experiences affect neuroendocrine and immune responses in other patient populations [23–29], an examination of active music to diminish emotional distress and improve positive health outcomes in children with cancer and parents is well justified and will address important gaps in our scientific knowledge about the use of music to improve health [30, 31].

The Active Music Engagement (AME) intervention uses interactive music play to counteract stressful qualities of the cancer treatment environment to reduce interrelated parent-child emotional distress and improve positive health outcomes during acute cancer treatment [32–34]. To counteract the lack of mechanistic understanding of music therapy approaches, we designed our current trial (R01NR019190) to examine AME’s effects on stress via Hypothalamic-Pituitary-Adrenal Axis (HPA-axis) activity and immune function (immunomodulatory cytokines). Within the context of pediatric cancer treatment there are special challenges that must be considered when measuring cortisol and immune function. In this manuscript we report our specific aims and study protocol. In addition, we identify and discuss three specific design challenges and how these were addressed.

## Specific aims

Purposes of this two-group, randomized, controlled trial are to examine mechanisms of effect and dose-response relationships of AME on child/parent stress over time. Specific aims are to:

### Aim 1

Compare the magnitude of change in child and parent cortisol levels between AME and control during Acute Lymphoblastic Leukemia (ALL) and T-cell Lymphoblastic Lymphoma (TLyLy) treatment.

###  Hypothesis 1.1

Compared to attention control, *children* in the AME group will have greater pre- to post-session percent decreases in cortisol.

###  Hypothesis 1.2

Compared to attention control, *parents* in the AME group will have greater pre-to post-session percent decreases in cortisol.

### Aim 2

Examine cortisol as a mediator of AME effects on child and parent outcomes during ALL and TLyLy treatment.

###  Hypothesis 2.1

Reductions in child and/or parent cortisol will mediate the effect of AME on child immune function.

###  Hypothesis 2.2

Reductions in child and/or parent cortisol will mediate the effect of AME on *child* emotional distress and quality of life.

###  Hypothesis 2.3

Reductions in child and/or parent cortisol will mediate the effect of AME on parent emotional/traumatic distress symptoms and quality of life.

### Aim 3 (Exploratory)

Examine the dose-response relationship of AME on child and parent cortisol during ALL and TLyLy treatment.

###  Hypothesis 3.1

While we make no hypotheses for this exploratory aim, we anticipate that AME effects may increase, decay, or remain constant over the course of treatment.

## Methods

Methods for this trial are grounded in our previously published work including several pilot studies [33–36] and a manuscript that details of our treatment fidelity strategies [37].

### Conceptual framework

Our conceptual framework (Fig. 1) is based on Robb’s Contextual Support Model of Music Therapy [32, 38], which is grounded in Self-Determination Theory [39] and further informed by Kazak’s Pediatric Medical Traumatic Stress Model [40], which provides a useful heuristic for understanding short and long-term consequences of pediatric cancer treatment for children and their parents. In our conceptual framework, recurring events related to cancer treatment (i.e., clinic visits, procedures) are viewed as stressful, potentially traumatic events.

**Fig. 1 Fig1:**
[figure not shown]
Conceptual Framework

Parent appraisal of events as traumatic or not traumatic is influenced by pre-existing factors that serve as *covariates* in our study. We based covariate selection on published research that indicates higher parent and child distress during cancer treatment is related to: (1) demographics (younger child/parent age, female parent gender, and lower socio-economic status/education) [41, 42], (2) higher parent/child distress with prior hospitalizations, and greater traumatic stress symptoms [5, 43, 44], and (3) disease and treatment characteristics (treatment intensity) [9–11, 45–49]. In addition, child and parent sex will be important covariates when analyzing our biological data based on evidence that sex hormones play a role in immune response [50, 51] and account for differences in salivary cortisol [52, 53].

We hypothesize that AME directly targets the *mediators* of child and parent biological stress (cortisol). Our study examines child and parent cortisol as mediators of AME intervention effect on *outcomes* for child (immune function, emotional distress, and quality of life) and parent (emotional distress, traumatic distress, quality of life). This study will allow us to determine *how* the AME intervention works at the biological level and the intersection of HPA-axis activity (cortisol) with reductions in emotional distress (emotional/traumatic stress; quality of life) associated with pediatric cancer treatment. Findings will have implications for the use of active music interventions to manage treatment-related distress in other populations.

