#### Preliminary analyses

Prior to hypothesis testing, we will calculate coefficient alpha as a measure of internal consistency reliability on all multiple-item scales. Construct validity will be assessed by calculating Pearson or Spearman correlations among scales to determine if correlations are in the expected direction. We will present descriptive statistics for the AME group and the attention control group with respect to demographic and baseline outcome variables. We will control for child and parent age, site, risk level (standard or high), greater distress with prior hospitalizations, greater traumatic stress symptoms, time of collection of pre-session cortisol, and child and parent sex in all models. Age, site, and risk level are stratification variables. Time of collection of pre-session cortisol will account for differences based on standard diurnal differences. Although time of collection will be similar within each child, there will likely be between-child differences in time of collection (e.g., some children will have collections in morning and some in afternoon) that we will control for in analyses.

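### Socio-economic status/education is named as a study covariate but is missing from the covariate list for all models, leaving a potential confounder of the Aim 2 cortisol-to-outcome path unadjusted

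*Protocol article*

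**What the plan says.** In the protocol article, the Conceptual framework section (text under Fig. 1) says that the parent's appraisal of events is "influenced by pre-existing factors that serve as *covariates* in our study". It gives the basis for choosing them: "We based covariate selection on published research that indicates higher parent and child distress during cancer treatment is related to" three groups of factors. The first group is "demographics (younger child/parent age, female parent gender, and lower socio-economic status/education"). The second is prior-hospitalisation distress and traumatic stress symptoms. The third is treatment intensity. Child and parent sex are added for the biological data.

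The Preliminary analyses section gives the working list. It begins "We will control for child and parent age, site, risk level (standard or high), greater distress with prior hospitalizations" and ends "greater distress with prior hospitalizations, greater traumatic stress symptoms, time of collection of pre-session cortisol, and child and parent sex in all models". Nothing in it corresponds to "lower socio-economic status/education".

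The Main analyses section says that each Aim 2 outcome model adjusts for the T1 value of the outcome and for the covariates already described. Table 2 places demographics among the antecedent factors, collected from the parent at T1 on a Family Information Form with three items. The items are not named.

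**The concern.** The list in Preliminary analyses is an explicit list for every model, and it follows the framework's wording closely. It reads as the operational version of the framework list with one factor lost, and no reason is given.

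The loss matters most in Aim 2, which the Sample size and power analysis section names as the primary goal and the driver of the sample size. AME is randomised; cortisol change is not. The estimated effect of cortisol change on distress, quality of life or cytokines therefore depends on adjustment for common causes of both. The framework says SES/education predicts parent and child distress, which is close to what hypotheses 2.2 and 2.3 measure. If it also predicts cortisol change, leaving it out biases the cortisol-to-outcome path and, through it, the indirect effect. Up to six models per outcome use the same list. Two differing lists also leave room to choose the covariates after the data are seen.

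**Working it through.** **Step 1. Set the two lists side by side.**

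| Factor in Conceptual framework | In Preliminary analyses list? |
|---|---|
| Child and parent age | Yes |
| Parent gender | Yes, as parent sex |
| SES/education | **No** |
| Distress with prior hospitalisations | Yes |
| Traumatic stress symptoms | Yes |
| Treatment intensity | Yes, as risk level (Study design and randomization equates the two) |
| Child sex | Yes |

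SES/education is the only named factor dropped. Site and time of cortisol collection are added.

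**Step 2. Reproduce the plan's own figures.** Inputs from Sample size and power analysis: 170 dyads retained; 13% of variation for AME to mediator (path a), 7% for mediator to outcome (path b), 2% for AME to outcome. Taking standardised paths as square roots gives a = √0.13 = 0.361, b = √0.07 = 0.265, c′ = √0.02 = 0.141. A simulated two-sided 5% Sobel test (4,000 runs) has 88.3% power, against 88% stated. The Aim 1 t-test with 85 per group and an assumed d of 0.5 has 90.0% power, against 90% stated. 170/0.75 = 227, against 228 stated. The model below therefore matches the plan's.

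**Step 3. Bias from the omission.** The article gives no association of SES with cortisol or with any outcome, so these are assumptions. Let r_M and r_Y be the standardised coefficients of SES on cortisol change and on the outcome. Randomisation makes SES independent of AME, so without SES in the model:

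bias in b = r_M × r_Y / (1 − a²) = r_M × r_Y / 0.87

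The last two columns are simulated Sobel rejection rates for the indirect effect when the true b is 0 (n = 170, 3,000 runs per setting, one mediator, no T1 outcome in the model).

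| r_M, r_Y | Bias in b | As share of 0.265 | Rejected, SES omitted | Rejected, SES included |
|---|---|---|---|---|
| 0, 0.3 | 0 | 0% | 3.3% | 3.5% |
| 0.1, 0.1 | 0.01/0.87 = 0.011 | 4% | 3.7% | 3.7% |
| 0.2, 0.2 | 0.04/0.87 = 0.046 | 17% | 6.0% | 3.6% |
| 0.3, 0.3 | 0.09/0.87 = 0.103 | 39% | 18.7% | 3.0% |

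Path a is about 0.36 in every setting, with or without SES. With SES in both equations and a true b of 0.265, the estimate of b stays at about 0.26 to 0.27 and power at about 0.88 to 0.92.

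**Step 4. Allow for the planned T1-outcome adjustment.** Assume that SES relates equally to the T1 and T2 outcome, and that these correlate 0.4 to 0.7 (the article gives no value). With the T1 outcome in the model and a true b of 0:

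- coefficients of 0.1: rejection of the indirect effect stays below 5%;
- coefficients of 0.2: bias falls to about 0.01 to 0.03, and rejection is about 4%;
- coefficients of 0.3: bias falls to about 0.03 to 0.06, and rejection is about 6 to 10%.

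The final test is a percentile bootstrap, not Sobel. The article expects it to have equal or greater power, so its rejection rates may be somewhat higher than those shown.

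**The case against.** A reader might infer that the plan leaves out a known confounder of the cortisol-distress path. The article does not support that. A confounder must relate to both mediator and outcome, and the cited research concerns factors to which "published research that indicates higher parent and child distress during cancer treatment is related to". The only factors tied to cortisol are sex, said to "account for differences in salivary cortisol", and time of collection. No link of SES to cytokines is stated either, which weakens the point for hypothesis 2.1. The mediator is also a percent change within the person, so SES would have to predict change in cortisol, not its level. This objection stands: SES/education is a potential confounder.

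A reader might also infer error rates of about 8% and 20% at correlations of 0.2 and 0.3. Those figures describe a test of path b alone, without the T1 outcome. Aim 2 tests the indirect effect and does adjust for the T1 outcome, so they are not the error rates of the planned analysis. This stands too. Other listed covariates, such as parent age, site and traumatic stress symptoms, may absorb more of any SES effect.

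Finally, the framework may be read as a literature rationale that is broader than the final model, or the Aim 2 reference to covariates already described as reaching back to the framework. The first reading is only a partial answer, because the framework says that these factors do serve as covariates in the study. The second leaves two different lists in force. Neither removes the mismatch.

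**Conclusion.** The point holds as an internal inconsistency with a possible, unquantified consequence for Aim 2. SES/education is named as a covariate and is the only named factor missing from the list for all models; nothing in the article explains or resolves this.

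The size of any bias rests entirely on assumed associations. It is zero if SES/education is unrelated to cortisol change and negligible at coefficients of 0.1. At 0.2 it is modest and falls to about 0.01 to 0.03 after T1-outcome adjustment. Clear inflation of the indirect-effect error rate needs coefficients near 0.3 on both sides, and the article gives no support for values that large. It would be wrong to conclude that the mediation results will be biased; they could be.

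Aim 1 and the AME-to-cortisol path are unaffected, and no sample-size figure changes. The reason to act is that the correction follows the plan's own covariate rationale and costs almost nothing.

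**What to change.** Add parent education, or the SES item on the T1 Family Information Form, to the covariate list in Preliminary analyses, at least in both the mediator and the outcome equation of every Aim 2 model. Have the Main analyses section refer to that list by name, so that only one covariate set is in force. First confirm that the three-item form records SES or education. The cost is one line of wording and one or two model degrees of freedom, with no change to the sample size.

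If the form does not record it, remove SES/education from the covariates named in the Conceptual framework section and state unmeasured SES/education as a limitation of the mediation analysis. If it was left out on purpose, give the reason. Settle this before outcome data are examined by group.

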### Study design and randomization

This study is a two group, stratified randomized controlled trial. The trial received Single Institutional Review Board Approval from Indiana University and is recruiting from three children’s hospitals in the United States. Children and one parent (enrolled as dyads) are stratified by child age (preschool 3–5 yrs; school-age 6–8 yrs), site, and treatment intensity (4 weeks standard risk B-cell ALL; 8 weeks high risk B-cell ALL, T-cell ALL, T-cell LyLy), and randomized in blocks of four to the AME intervention or attention control condition (audio-storybooks; ASB). See Fig. 2 for study schema.

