### Sample size and power analysis

We will recruit a total sample size of 228 child/parent dyads and assume 25% attrition to retain 170 child/parent dyads (85 dyads/group) at Time 2. The primary goal of this study is to examine mechanisms via the mediation effects of the AME intervention. We will use the percentile bootstrap method to estimate the indirect/mediated effect [55]. The sample size needed for this study is primarily driven by the power needed for the mediation hypothesis in Aim 2. Simulations of the two-path mediation model in Mplus [56] show that 170 subjects are needed to have 88% power to test the total indirect effect using the Sobel approach when the effect of the independent variable (AME in this case) on the mediator is at least medium (13% of variation explained), mediator on the outcome is between small and medium (7% of variation explained), and independent variable on the outcome is small (2% of variation explained). Via simulation, the Type I error with this sample size under a model that assumes no indirect effect is also less than 0.007, which will readily accommodate the multiple comparison adjustments planned below (e.g. with 7 cytokines a conservative Bonferroni adjustment would be 0.05/7 = 0.007). A sample size of 170 will also afford 90% power to detect a medium effect size for H1.1 and H1.2 based on a two-sample t-test with a two-sided alpha level of 0.05. Fitting models that allow for repeated measures across session will result in improved power. Using the percentile bootstrap method instead of Sobel should afford the same or greater power.

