### Recruitment and informed consent

This study has received single Institutional Review Board Approval from the Indiana University Institutional Review Board which serves a central IRB for all participating institutions. Project managers at each site recruit children/parents during a scheduled clinic visit during the induction phase of treatment. During initial approach, project managers provide initial study introduction/brochure and verify eligibility. For interested families, child/parent dyads are enrolled following written, informed parental consent for parent and child and written assent for children ≥ 7 years, following human subjects review committee requirements.

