### Outcome measures and data collection procedures

#### Parent (caregiver) report measures

Following informed consent, project managers at each site arrange a time for parents to complete baseline (T1) questionnaires during their first consolidation phase clinic appointment. A trained data collector administers questionnaires and remains available for questions. After completing T1 questionnaires, the project manager notifies the child/parent of their group assignment and schedules their first study condition session. Parents complete Time 2 questionnaires within 7 days of completing their last study session (session 4 for standard risk; session 8 for high risk).

The use of valid, reliable measures helps to ensure study rigor and reproducibility of results. All measures reflect careful consideration of psychometric properties, sensitivity to change, and response burden. Table 2 provides a list of measures, psychometrics, and administration schedule.

**Table 2 Tab2:** Measures

Variable(s)	Measure	# Items	Reliability Evidence	Admin. Schedule	Done By

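### A single published block size of four within site-based strata, with recruiters who also disclose the arm, lets up to about 30–33% of allocations be known with certainty at approach

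*Protocol article*

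**What the plan says.** The Abstract states that dyads "are stratified (by age, site, risk level) and randomized in blocks of four to the AME or attention control condition". The section Study design and randomization repeats the single block size (dyads are "randomized in blocks of four to the AME intervention or attention control condition") and lists the strata: dyads are "stratified by child age (preschool 3–5 yrs; school-age 6–8 yrs), site, and treatment intensity". The trial "is recruiting from three children’s hospitals in the United States", so site has three levels and every stratum lies inside one hospital.

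The section Recruitment and informed consent says: "Project managers at each site recruit children/parents during a scheduled clinic visit during the induction phase of treatment". The same role checks eligibility at that first contact. The section Parent (caregiver) report measures then says: "After completing T1 questionnaires, the project manager notifies the child/parent of their group assignment and schedules their first study condition session".

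The Masking process section covers families and the collectors of the baseline (T1) and Time 2 questionnaires. It states that saliva collectors are not masked, and it does not mention the project managers.

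**The concern.** When the block size is fixed and known, anyone who has seen the earlier assignments in a stratum can work out some of the later ones. A sealed or central list does not prevent this, because the prediction rests on past assignments and not on sight of the list. Here the role that approaches families is also the role that tells them their arm, so it builds up the local history as part of its work.

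What is at stake is selective entry. A recruiter who knows which arm comes next may, without intending to, approach or encourage families differently. There is room for judgement in how a family is introduced to the study, whether it counts as interested, and whether a parent is thought able to attend every session. If this happened, the arms could differ in distress or engagement before any session took place. The planned covariates and T1 scores would correct for that only as far as those factors are measured.

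**Working it through.** **Inputs**

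- Block size 4, one size only (Abstract; Study design and randomization).
- Equal allocation: the plan is to "retain 170 child/parent dyads (85 dyads/group) at Time 2", so each block holds two of each arm.
- Strata: 2 ages × 3 sites × 2 intensities = 12, or four per hospital.
- 228 dyads, an average of 228/12 = 19 per stratum. Equal strata are an assumption.

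**The plan's own figures.** The article gives no predictability figure. Its sample size is consistent: 170/0.75 = 226.7, rounded up to 227, against 228 stated; 228 × 0.75 = 171.

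**Step 1: complete blocks, all earlier assignments known.** The six possible orders are AABB, ABAB, ABBA, BBAA, BABA and BAAB, giving 24 places. The fourth place is determined in all six. The third is determined in two (AABB and BBAA). That is 8/24 = 33.3%. By position: (0 + 0 + 1/3 + 1)/4 = 1/3.

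**Step 2: strata of 19.** Four complete blocks give 4 × 4/3 = 16/3. The three places of the open fifth block add 0 + 0 + 1/3. The total is 17/3 = 5.67 of 19, or 29.8%. Over 12 strata this is 12 × 17/3 = 68 of 228. Simulated unequal strata give about 31%.

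**Step 3: delay in disclosure.** Families are approached during induction, and the arm is disclosed after T1. If the preceding dyad in the stratum is still undisclosed at approach, only the fourth place can be certain, and only when the first two match: (0 + 0 + 0 + 1/3)/4 = 1/12 = 8.3%. If the preceding two are undisclosed, the share is 0. The Discussion of biomarker strategy puts induction at 28 days and the start of consolidation 1–2 weeks later. With T1 at the first consolidation visit, approach and disclosure are then roughly 7 to 28 + 14 = 42 days apart. How often another family in the same stratum falls in that window depends on the accrual rate, which is not given.

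**Step 4: best guess, fixed blocks of four.** The chance of guessing right by position is 1/2, 2/3, 2/3 and 1. The mean is 2.833/4 = 70.8%. In a stratum of 19 it is (4 × 2.833 + 1.833)/19 = 69.3%.

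**Step 5: alternatives.** For varying sizes, the simulated recruiter sees every past assignment and knows which sizes are in use, but not their order.

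| Scheme | Certain | Best guess right |
|---|---|---|
| Fixed 4, stratum of 19 | 29.8% | 69.3% |
| Random 4/6, stratum of 19 | 5.7% | 68.0% |
| Fixed 4, complete blocks | 33.3% | 70.8% |
| Random 4/6, stratum of 20 | 5.8% | 68.5% |
| Fixed 6, complete blocks | 25.0% | 68.3% |

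A larger fixed block helps little; varying the size removes most of the certainty. The largest imbalance in an open block is half its size: 2 for a block of 4 and 3 for a block of 6.

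**The case against.** The strongest reply is that a third is a ceiling and not an expected figure, and this stands. It requires every earlier assignment in the stratum to be known at approach. The article does not say when a slot is drawn, how fast families accrue, or how many project managers each site has. That one person knows the whole history is an inference from the notifying role.

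Four other parts of the reply also stand.

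- **Deferral is a weak route to bias.** Enrolment must take place during induction, so delaying a family changes its arm only if another family in the same stratum takes the slot in those weeks. Selective approach or encouragement is the more plausible route.
- **Most eligibility criteria are factual.** A reader might infer that the recruiter could use the cognitive-impairment exclusion to steer entry. The Participants section has that decision made together with physicians and parents.
- **Adjustment helps.** Preliminary analyses lists age, site, risk level, prior hospitalization distress, traumatic stress and sex for all models. Main analyses adds the T1 outcome for Aim 2.
- **Blocks of four are conventional.** They limit imbalance in 12 small strata.

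The reply that this is a condensed article, with bias-reduction strategies described in a separate fidelity publication, carries less weight. The point rests on what the article fixes: one block size, and one role that both recruits and discloses. Concealment described elsewhere would not undo it. It would be answered only by varying block sizes or by recruiters who do not know past assignments. In either case the article's text would need correcting.

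**Conclusion.** The point holds as a design weakness that should be corrected. Up to about 30–33% of allocations could be known with certainty at approach. The lower figure assumes 12 equal strata of 19, and both assume that all earlier assignments in the stratum have been disclosed. With one preceding dyad undisclosed the share is about 8%, and with two it is zero. Since accrual is not given, the defensible range is 0 to 33%.

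A reader might go further and infer that about 70 families were in fact recruited with their arm known, or that the results are biased. The documents support neither. They show that prediction is possible, not that anyone predicted or acted on it. Nor do they show that allocation was unconcealed; the article does not describe concealment, and the problem does not depend on it.

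**What to change.** For the remaining allocations, use permuted blocks of randomly varying size (for example 4 and 6) within the same strata. Start each stratum's new list once its open block is full, so that no block is abandoned. Do not disclose the sizes to site staff, and do not publish them until accrual ends. Amend the sentence on blocks of four to match.

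Where existing staffing allows, have the therapist who delivers the session tell the family its arm, in place of the project manager who recruits. This matters because varying the sizes barely lowers best-guess accuracy (69.3% to 68.0% in strata of 19). What it removes is certain knowledge (29.8% to 5.7%). These figures are for whole strata under each scheme. Allocations already made are not protected, and the gain for the rest will be of this order, not exactly this.

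The cost is a new list for the remaining places and a short protocol amendment. The downside is that imbalance within an open block can reach 3 instead of 2. Strata, sample size and analysis are unchanged. If sizes already vary, or recruiters are already kept from the assignment history, only the description needs correcting.
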